### Blinding

Due to the nature of the intervention, neither participating healthcare professionals nor patients will be blinded to treatment. Investigators, outcome assessors and data analysts will be blinded to group allocation.

### Intervention: the PREVSAM model (intervention group)

The PREVSAM model includes:
a person-centred approachidentification of the patient’s attitudes towards responsibility for the management of musculoskeletal pain and clarification of responsibilities for the individual, health care, employer/Swedish public employer servicestructured, individualised, synchronised, rehabilitation based on interdisciplinary teamwork, continuous communication and regular coordination among all stakeholders, and a mutual philosophy of rehabilitationearly access to psychologist or psychotherapist to address psychosocial factorspossibility of early contact and collaboration with employer/workplace before sickness absence has occurred.

The person-centred approach entails planning the rehabilitation together in partnership with the individuals, and taking their resources and wishes into consideration [27]. Individualised, person-centred, rehabilitation within the PREVSAM model will be based on the patient’s narrative and constructed together with the interdisciplinary team based on the patient’s goals, attitudes of responsibility, and physical, psychological, and social resources. Workplace preconditions will be assessed, preferably based on the Convergence Dialogue Meeting [28] also used in a previous rehabilitation study [29], and employer responsibility will be highlighted, based on the Organisational and social work environment provisions from the Swedish Work Environment Authority (AFS 2015:4). Responsibilities for the different parts of the participant’s rehabilitation will be clearly assigned to the individual, health care, and employer or Swedish public employer service.

The interdisciplinary team is an important component of the PREVSAM model and will be comprised of the patient, a physiotherapist, an occupational therapist, and a psychologist/psychotherapist. If needed, contact with a general practitioner will be provided. If orthopaedic consultation or further investigations are needed, the participant can be referred to a physiotherapist with experience in orthopaedic triage for assessment and further management.

The PREVSAM model can also reach outside the healthcare system. Contacts can be taken immediately to facilitate collaboration to avoid sickness absence, usually with the employer/workplace, but could also involve the Swedish Public Employment Agency and the SSIA. Furthermore, a rehabilitation coordinator could be contacted, if necessary and available. This function within the healthcare system is specifically directed at internal coordination, external collaboration and individual patient support in questions related to sickness absence. In the PREVSAM model, adjustments of work parameters will be given early attention if there are work-related issues, rather than waiting for the patient to “get better” first. The individual rehabilitation should be planned to avoid a need for the patient to be on sickness absence (with the exception of preventive sickness cash benefit), as it has been suggested this might have a lock-in effect and increase the risk of long-term sickness absence [30]. Because each PREVSAM rehabilitation plan is individualised, the length of the rehabilitation period will differ for each individual, but will in most cases not exceed 8 weeks. If considered appropriate by the team and the patient, follow-up with the employer can take place.

Physiotherapists, occupational therapists and psychologists or psychotherapists will receive education, training and instructions in using the PREVSAM model at their workplace by the project coordinator before starting the study. They will also participate in workshops while the study is ongoing, together with the involved psychotherapist. The workshops aim to improve the teamwork, enable the practicing of the core values of the model, and provide discussions on possible ambiguities and difficulties, as well as sharing good experiences. They are expected to ensure adherence to the intervention protocol. The project coordinator will have regular contact with the participating centres through a monthly newsletter, e-mail or telephone on any practical or methodological questions.

### Comparison: treatment as usual (control group)

The participants randomised to TAU will receive management and treatment as usual, according to the choice of the responsible healthcare professional(s). Treatments may include information and advice, physical exercise, functional and ergonomic training, mobilisation/manipulation, relaxation, body awareness training, acupuncture, activity and pacing, stress management, lifestyle issue, etc. Treatment as usual was chosen as comparator because that is what the patient group is provided as best choice of treatment of today, and the study aims to evaluate whether a more comprehensive rehabilitation model would result in superior results. The type of consultation and interventions provided will be collected from the participant’s electronic medical record. Any other healthcare measures provided for the same diagnosis will be collected from the Region Västra Götaland’s healthcare utilisation database (VEGA).

The main components of the intervention and the comparator are summarised in Table 2.

**Table 2 Tab2:** PREVSAM model compared with treatment as usual

*PREVSAM model*	*TAU*
Medical history with a person-centred approach and structure	Medical history could include a person-centred approach
Physical examination	Physical examination
Identification and clarification of the patient’s attitudes towards responsibility for the management of musculoskeletal pain	
A rehabilitation plan with structured, individualised, synchronised rehabilitation based on interdisciplinary teamwork.	Individualised rehabilitation plan
Possibility of early access to psychologist or psychotherapist	Could be possible to see psychologist or psychotherapist
Possibility of early contact and collaboration with employer and workplace	

TAU = treatment as usual

### Outcomes

#### Primary outcome

##### Sickness absence

Sickness absence will be measured using the proposed outcome measures from the Swedish Social insurance report 2016:9 [31]. These measures are based on sick-leave data at the individual level (including diagnoses) of all sick-leave spells longer than 14 days in which sickness cash benefits were provided by the SSIA. Data will be retrieved from the MiDAS database (preventive sickness absence will be excluded as this might be part of intervention). All sickness absence is planned to be analysed, but the main focus is on sickness absence relevant to musculoskeletal pain. Sickness absence was chosen as primary outcome because it is a frequent consequence of musculoskeletal pain, and it is of relevance for both the individual, the employer and society to measure and target this outcome when testing and implementing a new rehabilitation model for this patient group.

Sickness absence will be operationalised as:
Number and proportion of individuals who were on sickness absence and/or the number and proportion of individuals who remain in full- or part-time work during the follow-up period.Number of gross and net sick-days during the follow-up period.Time to first sickness absence spell.

Short-term sickness absence (≤ 14 days) is not reported to the SSIA among employed participants. They have sick pay from their employer the first 2 weeks of a sick-leave spell. Thus, short-term sickness absence will be measured using self-reported responses to weekly text messages via mobile phone (SMS-Track ApS, Denmark, www.sms-track.com). The participants will enter a number from 0 to 7 in response to the question “Have you been absent from work during the past week due to your musculoskeletal pain, and if so for how many days?”. However, unemployed participants have sickness benefits from the SSIA from the second day of a sick-leave spell.

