### Statistical analyses

Primary outcomes are sickness absence and sick days, where the first outcome is binary and the second one is continuous and most likely skewed [47]. Sick leave regardless of reason will be retrieved. However, sick leave for diseases of the musculoskeletal system and connective tissue is of specific interest. Sample size calculations will be based on the general assumptions that we want a power of 80% and that statistical significance is set to α = 0.05. For the outcome sickness absence, the difference between the proportion of sickness absence = yes/no will be compared between the intervention (PREVSAM model) and control (TAU) group. We assume that approximately 30% in the control group will have sickness absence = yes at least one time during the 12 month follow-up period [48]. If the percentage of sickness absence = yes in the intervention group is assumed to be 15% or 20%, then the sample size in each group needs to be 312 individuals and 132 individuals, respectively. To detect a difference of 15% (30% with sickness absence in control group and 15% with sickness absence in intervention group), a total sample size of 264 (132 individuals in each group) would give approximately 80 cases to analyse for the primary outcome sick days. This would enable us to estimate 8 parameters in a logistic regression analysis. This would mean a power of about 75% to detect a difference of at least 0.6 Ln (sick days), if the standard deviation for Ln (sick days) is assumed to be 1. This is equal to a scenario with mean sick days of about 35 in the intervention group (PREVSAM model) and 68 in the control group (TAU). This would enable us to perform linear regression analysis adjusting for several covariates and estimating about 7 parameters. To summarise these calculations and allowing for dropouts, randomisation of 200 individuals to each group is required. An interim analysis will be performed for the primary outcome when 50% of patients have been randomised and have completed the 12 months follow-up. At the same time-point it might be possible to perform the short-term follow-up analyses. The interim analysis will be performed by a statistician, blinded to the treatment allocation. The statistician will report and discuss the results of the interim analysis with the steering committee in a joint meeting. The steering committee decides on the continuation of the trial.

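### Preventive sickness benefit is left out of the primary outcome for a reason tied to one arm, and no analysis that counts it is described

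*Protocol article*

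**What the plan says.** Under Outcomes, Sickness absence, the protocol article builds the primary outcome on "all sick-leave spells longer than 14 days in which sickness cash benefits were provided by the SSIA", retrieved from the MiDAS database. It then qualifies this: "preventive sickness absence will be excluded as this might be part of intervention". Three measures follow from these data: the proportion with absence (or remaining in work), gross and net sick days, and time to first spell.

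The section on the PREVSAM model says that individual plans should keep the participant off sickness absence, "with the exception of preventive sickness cash benefit". The section on TAU leaves care to the responsible clinician and does not mention preventive benefit. Nor does Table 2, which compares the two arms.

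Statistical analyses describes no analysis that includes preventive benefit. The Outcomes section does say that all sickness absence will be analysed. Statistical analyses explains this as absence for any reason, so it concerns diagnosis and does not bring the excluded benefit back.

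**The concern.** The reason given for the exclusion is the allocated treatment, so the protocol itself allows that the benefit may be used as part of PREVSAM. A PREVSAM participant whose compensated absence is all preventive benefit is scored as not absent, adds no gross or net days and has no first spell. A TAU participant with the same time away on ordinary sickness benefit counts on all three measures.

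If that pattern occurs, the data cannot separate absence that was prevented from absence that moved to another benefit type. The first research question asks whether PREVSAM prevents sickness absence, so the distinction matters. The treating teams who make the plans are not blinded. The register outcome is the part of the trial least exposed to unblinded self-report, which makes the neutrality of its definition more important.

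**Working it through.** **Inputs from the protocol article (Statistical analyses).** The control rate is stated as "approximately 30% in the control group will have sickness absence = yes at least one time" during 12 months. The design values are "we want a power of 80% and that statistical significance is set to α = 0.05"; sidedness is not stated, and I take two-sided. The planned contrast is 30% against 15% with 132 per group, and 200 per group are to be randomised.

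**Reproducing the plan's figure.** With d = p1 − p2 and p̄ the mean of the two rates, the usual two-proportion formula is

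n = [1.96·√(2p̄(1−p̄)) + 0.842·√(p1(1−p1)+p2(1−p2))]² / d².

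It gives 121 per group for 30% against 15%. With the continuity correction, n/4·[1+√(1+4/(n·d))]², it gives 134, close to the stated 132. For 30% against 20% the corrected figure is 313, against a stated 312. The plan's inputs can therefore be used as they stand.

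**Assumption that the documents do not supply.** Let f be the share of absentees in an arm whose compensated absence over the whole 12 months is preventive benefit only. No value of f is given for either arm.

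**Calculation.** Suppose there is no true effect, with 30% absent in both arms when every benefit type is counted. The observed rate in each arm is 0.30·(1−f). With d now TAU minus PREVSAM, the two-sided rejection probability of the unadjusted pooled test is

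Φ[(d − 1.96·se0)/se1] + Φ[(−d − 1.96·se0)/se1],

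where se0 = √(2p̄(1−p̄)/n) and se1 = √((pP(1−pP)+pT(1−pT))/n), with P for PREVSAM and T for TAU.

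Worked case, f = 0.25 in PREVSAM, 0 in TAU, n = 200:
- pP = 0.225, pT = 0.30, d = 0.075, p̄ = 0.2625
- se0 = 0.0440, se1 = 0.0438
- (0.075 − 0.0862)/0.0438 = −0.256, so the probability is 0.399; the other tail is negligible.

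| f PREVSAM | f TAU | Observed rates (PREVSAM vs TAU) | Apparent difference (points) | Rejection, 132 per arm | Rejection, 200 per arm |
|---|---|---|---|---|---|
| 0 | 0 | 30% vs 30% | 0 | 0.050 | 0.050 |
| 0.10 | 0.10 | 27% vs 27% | 0 | 0.050 | 0.050 |
| 0.10 | 0 | 27% vs 30% | 3 | 0.084 | 0.102 |
| 0.20 | 0.10 | 24% vs 27% | 3 | 0.086 | 0.106 |
| 0.20 | 0 | 24% vs 30% | 6 | 0.195 | 0.271 |
| 0.25 | 0 | 22.5% vs 30% | 7.5 | 0.282 | 0.399 |

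The error depends on the difference in use between the arms. Equal use leaves the test at its nominal level.

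**Other primary measures.** Total gross and net days fall, and time to first counted spell lengthens, in whichever arm uses the benefit more. The planned regression of days is limited to participants with at least one spell. There, a shift also changes who is analysed, so its direction is less certain.

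**The case against.** The strongest reply is that the exclusion is a reasoned and disclosed choice. If preventive benefit is time spent in treatment, counting it would score delivery of the intervention as failure and bias the result against PREVSAM. Neither definition is free of bias. This stands, and it is why the stated definition should remain.

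The rule also names no arm. Preventive days in TAU are dropped too, and ordinary sick leave in PREVSAM counts. TAU clinicians are not barred from using the benefit. This stands as well: bias needs differential use, and that use must replace ordinary leave. The documents show neither.

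Misclassification on the yes/no outcome needs a participant to have nothing but preventive benefit for 12 months. PREVSAM rehabilitation mostly lasts no more than 8 weeks, and any ordinary registered spell in the rest of follow-up still counts. That argues against large shares.

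The weekly text messages ask about days away from work for musculoskeletal pain without regard to benefit type, so they are a partial check. They are self-reported by unblinded participants, intended for short-term absence, and secondary in the abstract, so they do not settle the matter.

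Finally, sensitivity analyses are often left to an analysis plan, and their absence from an article is not in itself a fault. The point here is narrower: the article fixes an exclusion in the primary outcome whose stated reason is the treatment in one arm.

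A reader might infer that PREVSAM steers participants towards preventive benefit. The text only exempts it from a general aim and says that it might be part of the intervention; no instruction to use it appears.

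**Conclusion.** The point holds as a conditional risk to the primary comparison. If preventive benefit is used more in PREVSAM and replaces ordinary sick leave, the proportion absent, the total gross and net days and the time to first spell would all favour PREVSAM. The documents describe no analysis that would reveal it.

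The size is unknown. With 30% true absence in both arms, no shift in TAU, an unadjusted two-sided test and 200 analysed per arm, a 10% shift doubles the nominal 5% error to about 10%, and a 25% shift raises it to about 40%. These shares are assumptions.

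A reader might go further and infer that the whole planned effect could be an artefact, because a shift of half the PREVSAM absentees turns 30% into 15%. The arithmetic is correct, but nothing in the documents supports a share of that size with none in TAU. Bias in the productivity-loss results is also not shown, since no section applies the exclusion there.

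**What to change.** Keep the primary outcome as defined and add three things:
- Retrieve preventive benefit from MiDAS for both arms.
- Report preventive spells and days by arm.
- Pre-specify a sensitivity analysis of the primary measures that counts all SSIA-compensated absence including preventive benefit. Fix it before any outcome data are examined, including those for the interim analysis.

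State in advance that if the two analyses differ, the result will be interpreted as a possible shift between benefit types. If use is rare or balanced, the added analysis will show that and strengthen the result.

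The cost is one further extraction from a register already in use and one repeated analysis; recruitment, treatment and follow-up do not change. The downside is that some preventive days are treatment time, so the inclusive effect may be smaller. It should be read as a bound on the effect and should not be a condition for the primary claim.

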#### Secondary outcomes

##### Patient-reported work ability

As registered sickness cash benefit for sick-leave not always is equivalent to the self-perceived ability to work, a single-item question of the Work Ability Index (WAI) [32], “current work ability compared with the lifetime best” will also be used. This question has been found to correspond well to WAI categories of the full instrument [33].

##### Patient-reported pain status

*Pain frequency* during the previous week will be measured using a 4-point Likert scale from 1 (always/nearly always) to 4 (rarely). *Pain duration* (0–1 week (w), 2–3 w, 4–5 w, 6–7 w, 8–9 w, 10-11w, 12–23 w, 24–35 w, 36–52 w or more than 52 w) will be registered. *Pain intensity* during the previous 7 days will be measured using an 11-point numeric rating scale (NRS) [34] anchored by “no pain at all” and “worst imaginable pain”). The NRS has been shown to have better responsiveness, ease of use, compliance rate, and applicability than a visual analogue scale and a verbal rating scale [35]. *Number of pain sites* the previous 7 days will be measured using a predefined manikin where the patient marks the location of their pain on an anatomical sketch of a human body.

##### Patient-reported self-efficacy

A 2-item short form of the Pain Self-Efficacy Questionnaire (PSEQ-2) will be used to measure changes of beliefs held regarding the possibility to carry out certain activities even when experiencing pain. The PSEQ-2 is a short form of the Pain Self- Efficacy Scale (PSEQ), which is a well-established and widely used measure of self-efficacy in people with chronic pain [36]. The PSEQ-2 has evidence of validity and reliability in people experiencing chronic pain [37]. Items 5 and 9 from the PSEQ are used in PSEQ-2. PSEQ-2 will be translated into Swedish before use, following the procedure described by Beaton et al. [38]. One informed and one uninformed Swedish native translator will translate the two items, response options, and questionnaire instructions. They will do a written report about difficulties and challenges with the translation, compare their versions, and merge their translations into a synthesised version. An observer will notice how they reach consensus. A synthesised translation will be back translated into English by two English native translators, and a written report will be made for each version. An expert committee will read the reports and the two versions, and discuss to reach consensus and produce a final Swedish version of the questionnaire [38].

The General Self-Efficacy Scale (GES) will be used to assess the strength of an individual’s belief in his/her own ability to respond to difficult situations and to execute a course of action to a desired outcome [39]. It consists of 10 items rated on a 4-point Likert scale (“not at all true” to” exactly true”). The Swedish translation of the GES has proven to be a reliable indicator of perceived general self-efficacy [40].

##### Patient-reported health-related quality of life

The European Quality of Life-5 Dimensions Questionnaire (EQ-5D-5L) will be used to assess health-related quality of life [41]. The EQ-5D has evidence of validity and reliability in different musculoskeletal disorders [42].

##### Patient-reported risk for sickness absence

The ÖMPSQ-SF will be used primarily as a screening instrument for the planned study [26], but also as an outcome measure for *changed risk* (proportion lowering their risk by scoring < 40 p at follow-up). The original Örebro Musculoskeletal Pain Screening Questionnaire (ÖMPSQ) was developed as a screening questionnaire for identifying patients at risk of developing persistent back pain problems, and has been shown to have acceptable reliability and validity [43]. It is often described as predictive for persistent pain, but studies have usually evaluated the predictive validity of the questionnaire for sickness absence [26, 43]. The ÖMPSQ-SF is self-administered and includes item 7, 9, 13–16, 19–21 and 25 from the original ÖMPSQ. The item contains a statement or an assertion which the respondents rate on 11-point Likert scales from 0, referring to absence of impairment, to 10, severe impairment. A cut-off of 50 points has been recommended to identify those of higher risk of future disability and sickness absence [26]. However, clinical experience as well as recent studies have shown that a cut off of 40 points might be better to use [29]. Although the instrument was primarily developed for people with back pain, the questions regarding musculoskeletal pain are general and can be used for other regions of musculoskeletal pain. The short version has been shown to be appropriate for clinical and research purposes, since it is nearly as accurate as the original, longer version [26].

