### Aims

The aim of the study is to evaluate effects of an early intervention, the PREVSAM model, on the prevention of sickness absence and development of persistent pain in at-risk patients with musculoskeletal pain. The study will also evaluate effects of the PREVSAM model on patient-reported work ability, risk for sickness absence, musculoskeletal pain status, self-efficacy, health-related quality of life, physical disability, depression and anxiety symptoms, and drug consumption. Cost-effectiveness of the model will be evaluated.

Research questions:

Q1: Is the PREVSAM model more effective in preventing sickness absence, compared with treatment as usual, in patients with musculoskeletal pain who have been identified to be at risk for sickness absence?

Q2: Do patients participating in the PREVSAM model report higher work ability, improved pain status, better self-efficacy, less physical disability or higher health-related quality of life, compared with those who receive treatment as usual at follow-up?

Q3: Is there a patient-reported reduced risk (using the ÖMPSQ score) for sickness absence in patients participating in the PREVSAM model, compared with those who received treatment as usual at follow-up?

Q4: Can any effects be seen in regard to anxiety and depression symptoms or drug consumption in patients participating in the PREVSAM model, compared with those who receive treatment as usual?

Q5: Is the PREVSAM model more cost-effective compared with treatment as usual?

The study hypothesis is that a person-centred rehabilitation, illuminating and emphasizing responsibilities, using interdisciplinary teamwork which can also include collaboration with the employer and/or workplace, in an early stage before symptoms are manifest and consequences in form of sickness absence have become established, will be more effective than treatment as usual in prevention of sickness absence.

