### Study population and setting

Adult individuals in Region Västra Götaland who seek health care for musculoskeletal pain at primary care rehabilitation centres or primary care healthcare centres are potentially eligible for inclusion. A list of study centres will be available from the corresponding author on request. Inclusion and exclusion criteria for study participation are described in Table 1.

**Table 1 Tab1:** Inclusion and exclusion criteria for study participation

*Inclusion criteria*	*Exclusion criteria*
Aged ≥18 years	Pain not primarily generated from the musculoskeletal system
Understand Swedish sufficiently to be able to fill out the questionnaires	Sickness cash benefit more than 30 days during the last 12 months due to musculoskeletal pain
Having a paid job or receiving parental leave benefits, unemployment benefits or student aid	Full disability pension or retired due to age
Musculoskeletal pain for less than 3 months during the current episode	Pregnancy
Risk for development of persistent musculoskeletal pain and disability, indicated by a score ≥ 40 on the ÖMPSQ-SF	Red flag disorders such as malignancy/ cancer, acute major traumas such as multiple fractures (less than 6 months ago) or infection, spinal cord compression/cauda equina
Independently mobile (with or without aids), to be capable of participating in intervention	Severe mental illness, ongoing substance abuse disorders

For inclusion, participants will be screened using the Örebro Musculoskeletal Pain Screening Questionnaire Short Form (ÖMPSQ-SF) [26]. A total score below 40 points on the ÖMPSQ-SF indicates a low risk for development of manifest problems and sickness absence, while scores over 40 points indicate an increased risk. In the screening process we will select individuals with ÖMPSQ-SF score equal to or greater than 40.

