Group characteristics will be presented as mean and standard deviations, median and 25th and 75th percentile or the number and percentage. For the primary outcomes descriptive analyses for sickness absence for the two groups will be presented according to recommendations [31]. The sickness absence will be presented with number of individuals who had sickness absence during the follow-up period. Proportions of individuals with sickness absence per month will be presented. The number of sick days (gross and net) with sickness benefit during the follow-up periods will be presented with mean and median values. For participation in work life additional measures will be presented with descriptive statistics regarding time to sick-leave spell for musculoskeletal pain. Number of days before a sick leave spell > 14 days occurs and number and duration of sick-leave spells per individual will be presented for gross and net days. Outcomes will be analysed according to intention-to-treat. Multivariable logistic regression analysis will be used for the primary outcome sickness absence during the follow-up period [1], not being sickness absent (0) adjusted for confounders. Multivariable linear regression analyses, or possibly quantile regression, will be used to evaluate differences between groups for sick leave days, among those have at least one sick leave spell. All other measurements will be analysed by calculating raw differences between baseline and follow-up assessments. Parametric and non-parametric tests will be used depending on data level and distribution. Sub-group analyses can be performed in regard to characteristics of interest, such as diagnosis or sick-leave. The level of significance is set to *p* < 0.05. Relevant statistical programs will be used for the statistical analyses, for example the IBM SPSS, SAS, STATA.

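### Changed risk (Q3) is defined by the same ÖMPSQ-SF cut of 40 that admits participants, the general analysis rule implies a different measure, and the protocol does not say which one answers the question

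*Protocol article*

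**What the plan says.** Four places in the protocol article bear on this.

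- **Aims, Q3** asks: "Is there a patient-reported reduced risk (using the ÖMPSQ score) for sickness absence in patients participating in the PREVSAM model", compared with treatment as usual. It refers to the score and mentions no cut.
- **Study population and setting** fixes entry: "In the screening process we will select individuals with ÖMPSQ-SF score equal to or greater than 40".
- **Patient-reported risk for sickness absence** gives the only outcome definition for changed risk, the "proportion lowering their risk by scoring < 40 p at follow-up". The same section says that the short form "includes item 7, 9, 13–16, 19–21 and 25 from the original ÖMPSQ", each of which respondents "rate on 11-point Likert scales from 0, referring to absence of impairment, to 10, severe impairment". It also reports that "A cut-off of 50 points has been recommended to identify those of higher risk of future disability and sickness absence", and then gives reasons for preferring 40.
- **Statistical analyses**, after setting out the models for the primary outcomes, states: "All other measurements will be analysed by calculating raw differences between baseline and follow-up assessments". No exception is made for the ÖMPSQ-SF.

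The abstract lists risk for sickness absence among the secondary outcomes at 1, 3, 6 and 12 months. No sample size or power is stated for it.

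**The concern.** A responder definition whose threshold is also the entry threshold treats participants unevenly. Someone who enters at 40 needs to lose one point. Someone who enters at 85 can lose 40 points and still be counted as not having lowered their risk. Some of those who start just above the line will cross it through measurement error alone. The definition itself makes no use of the entry score.

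Reducing a 0–100 score to a yes/no result also costs precision, which matters for one of the five named research questions.

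The general rule of raw differences adds a second problem. It points to a continuous change score, while the outcome section points to a proportion. The two can disagree: one may reach significance while the other does not. Unless one is named in advance as the answer to Q3, the reading of the result stays open until the data are seen.

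**Working it through.** **1. The scale.** The items listed are 7, 9, 13, 14, 15, 16, 19, 20, 21 and 25, which makes 10. Each is scored 0–10, so the total runs from 0 to 100 and entry scores run from 40 to 100.

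**2. What the cut does** (success means a follow-up score below 40):

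| Entry | Follow-up | Fall | Counted as lowered risk |
|---|---|---|---|
| 40 | 39 | 1 | yes |
| 85 | 45 | 40 | no |
| 80 | 40 | 40 | no (40 is not below 40) |
| 100 | 40 | 60 | no (largest fall that can fail) |

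This step needs no assumption.

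**3. The plan's own figures.** There is no power figure for this outcome to reproduce. The group sizes used below are the plan's: 132 per group needed and 200 per group randomised. The 132 comes from the primary outcome (30% against 15%, 80% power, α = 0.05, taken as two-sided). The standard two-proportion formula gives 121, or 134 with continuity correction, which agrees with 132 to within 3%.

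**4. Cost of splitting a score, in general.** For a normal score cut so that a proportion p lies below, the relative efficiency is E = φ(z_p)² / [p(1 − p)]. If the uncut score has 80% power, the split has power Φ(2.80·√E − 1.96).

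| p below 40 | E | Sample-size inflation 1/E | Power in place of 80% |
|---|---|---|---|
| 0.5 | 0.637 | 1.57 | 61% |
| 0.3 or 0.7 | 0.576 | 1.74 | 57% |
| 0.2 or 0.8 | 0.490 | 2.04 | 50% |
| 0.1 or 0.9 | 0.342 | 2.92 | 37% |

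This isolates the effect of dichotomising, because neither side is adjusted for baseline.

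**5. Simulation with entry at 40 or more.** All inputs are assumed: whole-number scores; baseline normal with mean 50 and SD 10, or mean 55 and SD 12, truncated at 40; slope of follow-up on baseline 0.6; residual SD 14; true difference 5 points; mean fall in the control arm 5 to 25 points.

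| n per arm | Proportion below 40 | Raw change | Baseline-adjusted score |
|---|---|---|---|
| 132 | 45–61% | 79–81% | 80–85% |
| 200 | 61–77% | 91–94% | 93–95% |

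**6. Check by formula.** Power ≈ Φ(5/SE − 1.96), with SE = SD·√(2/n).

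- Adjusted score, n = 132: SE = 14·√(2/132) = 1.723; 5/1.723 = 2.90; power Φ(0.94) = 83%.
- Adjusted score, n = 200: SE = 1.400; 5/1.400 = 3.57; power Φ(1.61) = 95%.
- Raw change, SD about 14.5, n = 132: SE = 1.785; 5/1.785 = 2.80; power Φ(0.84) = 80%. At n = 200: SE = 1.450; 5/1.450 = 3.45; power Φ(1.49) = 93%.
- Proportion, 41.5% against 55.0% (one simulated setting), n = 132: SE = √(2 × 0.4825 × 0.5175/132) = 0.0615; 0.135/0.0615 = 2.195; power Φ(0.235) = 59%, against 61% simulated.

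**7. A second set of assumptions.** Take follow-up SD 15, baseline correlation 0.3–0.6, 160 per arm and the same 5 points. Simulation gives 56–67% for the proportion and 87–97% for the adjusted score. By formula the residual SD is 15·√(1 − r²), which is 14.3 at r = 0.3 and 12 at r = 0.6, giving 88% and 96%. With SD 12 and 200 per arm, SE = 1.2 and 5/1.2 = 4.17, so power is Φ(2.21) = 99%. This is the top of the 80–99% range.

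**The case against.** The strongest reply is that the plan does not rest on the cut. A reader of the outcome section might infer that the proportion below 40 is the only analysis planned for Q3 and that the baseline score goes unused. The documents do not support that: the raw-difference rule, read literally, covers this score and uses its baseline, and Q3 itself speaks of the score. If that rule governs, adjusting for baseline adds only a few points of power, as step 5 shows. This stands. It turns the problem into one of two competing analyses, which still needs settling.

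A reader might also infer that regression to the mean biases the result. It does not. It acts in both randomised arms, so the comparison between them stays valid.

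Nor does the cut throw away most of the information. At responder rates between 30% and 70%, 57–64% of the efficiency of the unadjusted score is kept (1/1.74 and 1/1.57).

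The power gaps in steps 5 and 7 set an unadjusted test of proportions against an adjusted model, so part of each gap comes from adjustment. That is fair. Step 4 and the raw-change column show that most of the gap remains without adjustment.

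The value 40 is argued for and used consistently. Asking whether a person admitted as at risk is still at risk by the trial's own line is coherent and easy to explain. This is a reason to keep the proportion, though not as the main comparison.

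Finally, model details for a secondary outcome are often left to an analysis plan that is not shown. That covers the choice of covariates. It does not cover two statements in this article that point to different measures.

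**Conclusion.** The point holds in limited form and is minor. It is certain from the text that the sole outcome definition for changed risk uses the entry cut, so a 1-point fall can succeed and a 40-point fall can fail. It is also certain that the general rule of raw differences, taken literally, points to a different measure, and that the article does not say which one answers Q3.

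The loss of power is conditional. With an assumed 5-point effect and 132 to 200 per arm, the responder test has roughly 45–77% power, against about 80–99% for the baseline-adjusted score and 79–94% for raw change. The direction is the same in every setting examined. The size depends on a mean, SD, correlation and effect that the documents do not give, for a secondary outcome on which no power is claimed. Nothing here affects the primary outcome or the validity of the randomised comparison.

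**What to change.** Reconcile the section on patient-reported risk for sickness absence with the Statistical analyses section. Suggested wording: *The main comparison for Q3 is the difference between arms in continuous ÖMPSQ-SF score at each follow-up, adjusted for the baseline (screening) score. The proportion scoring below 40 is reported by arm as a supporting summary; if it is tested, the screening score is included as a covariate.*

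Also state that the raw-difference rule does not govern this outcome.

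The cost is a change of wording made before the data are analysed. The screening score is known for every participant and the follow-up scores are already planned, so no new data are needed. The responder proportion is still reported.
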